### Sample size

Because this is a registry-based observational study, the target sample size was set based on feasibility and the planned secondary analyses. Across the six participating sites, approximately 370 patients are expected to meet eligibility criteria. Assuming a participation rate of 70%, the registry aims to enroll approximately 250 participants. Allowing for 20% attrition due to mortality or institutionalization, the expected final analytic sample is approximately 200 participants.

For logistic regression of response, we prespecified response as a decrease of ≥1 point in the K-ADL score from baseline to 1 year. Because a validated minimal clinically important difference (MCID) for the K-ADL has not been established, this threshold was selected pragmatically, informed by indirect evidence from related basic ADL measures [12,13]. Based on this definition, we assumed a response rate of 35–45% according to a previous rehabilitation trial reporting recovery of ADL performance at 12 months [14]. With an expected final analytic sample of 200 participants, this would yield approximately 70–90 responder events, which is sufficient to support up to eight prespecified covariates based on an events-per-variable ratio of approximately 10 [15,16]. The prespecified covariates are age, sex, comorbidity count, baseline K-FRAIL, baseline K-ADL, Five Times Sit-to-Stand Test (FTSST), NRS, and service utilization, selected based on clinical relevance and prior evidence [17–20].

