### Outcomes

The primary outcome is the change in K-ADL from baseline to 1 year. K-ADL is a 7-item measure (score range 7–21), where lower scores indicate greater independence [18]. Secondary outcomes assessed at the 1-year interval include frailty status according to K-FRAIL (0: robust, 1–2: pre-frail, 3–5: frail) [17], changes in medication use (polypharmacy and deprescribing patterns), and patient satisfaction measured once at 1 year using the CSQ [21]. AIP indicators (mortality, long-term hospitalization >30 days, and admission to long-term care facilities) are recorded upon occurrence [22–24], while chronic pain intensity measured by the NRS (0–10) is assessed at every visit. Additional outcomes and covariates will be derived from pilot program–mandated administrative records, including the Comprehensive Assessment and Care Plan and visit logs, which capture sociodemographic characteristics, health and functional status, and service delivery details.

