### Safety considerations

As an observational registry without experimental interventions, study-related risk is expected to be minimal. Mortality, long-term hospitalization (>30 days), and admission to a long-term care facility will be tracked as key events relevant to safety and sustainability. If such an event occurs, follow-up will be discontinued and the reason recorded in the CRF. Given the minimal-risk nature of the study, a formal data monitoring committee will not be convened; safety oversight will be conducted through regular investigator meetings and the independent monitoring process described above.

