### Statistical analysis

Analyses will be performed in R (version 4.5.2) using RStudio (version 2025.09.2). All tests will be two-sided with α = 0.05. Baseline characteristics will be summarized using descriptive statistics.

The primary outcome (change in K-ADL from baseline to one year) will be evaluated in the overall cohort using a paired t-test or Wilcoxon signed-rank test, depending on distributional assumptions. Because the registry includes both newly enrolled and pre-existing patients, baseline functional status and prior exposure to KM-HMC services may differ between participants. Baseline characteristics, including baseline K-ADL, will therefore be compared between newly enrolled and pre-existing patients. To assess the robustness of the findings in the presence of this mixed cohort structure, a sensitivity analysis will be performed using multivariable linear regression with change in K-ADL as the dependent variable, adjusting for baseline K-ADL, months of prior service exposure, and registration status (new vs. existing). No interim analysis is planned.

Longitudinal NRS (measured at each visit) will be analyzed using a linear mixed-effects model with a random intercept and time treated as a continuous variable. Other secondary continuous outcomes (e.g., K-FRAIL) will be analyzed using paired t-tests or appropriate non-parametric alternatives.

Factors associated with response will be examined using multivariable logistic regression, with response operationally defined as a decrease of ≥1 point in the K-ADL score from baseline to 1 year. Participants who die or are permanently institutionalized during follow-up will be classified as non-responders to reduce attrition-related bias. Prespecified covariates are age, sex, comorbidity count, baseline K-FRAIL, baseline K-ADL, FTSST, baseline NRS, and service utilization frequency. Model fit, multicollinearity, and influential observations will be assessed using standard diagnostics.

Missing data will be handled using multiple imputation by chained equations (MICE), creating 20 imputed datasets and including auxiliary variables related to health status and service use; estimates will be pooled using Rubin’s rules. Exploratory analyses using administrative data (e.g., service utilization patterns and detailed assessments) will be conducted for hypothesis generation, with methods selected according to the research question and data structure.

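### The primary K-ADL change has no rule for participants whose follow-up ends at death, long hospitalisation or facility admission, so it describes those who stayed at home rather than the overall cohort

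*Protocol article*

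**What the plan says.** Outcomes defines the endpoint: "The primary outcome is the change in K-ADL from baseline to 1 year". It therefore needs a score at 1 year. On direction and range: "K-ADL is a 7-item measure (score range 7–21), where lower scores indicate greater independence". A negative change is improvement, and no value is assigned to death.

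Safety considerations lists the events: "Mortality, long-term hospitalization (>30 days), and admission to a long-term care facility will be tracked as key events". It then adds: "If such an event occurs, follow-up will be discontinued and the reason recorded in the CRF".

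Sample size plans for the loss: "Allowing for 20% attrition due to mortality or institutionalization, the expected final analytic sample is approximately 200 participants".

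Statistical analysis evaluates the primary change in the overall cohort with a paired t or signed-rank test. Its general missing-data rule is: "Missing data will be handled using multiple imputation by chained equations (MICE), creating 20 imputed datasets". The sentence goes on to include auxiliary variables on health status and service use. The one rule for events sits in the paragraph on the logistic model: "Participants who die or are permanently institutionalized during follow-up will be classified as non-responders to reduce attrition-related bias". The only sensitivity analysis for the primary outcome concerns new versus existing patients.

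**The concern.** The people who lose their 1-year score lose it because something bad happened to them. The plan acknowledges this for the responder model, where it gives attrition bias as the reason for its rule, but has no matching provision for the primary outcome. Only two routes can be read from the text: leave these participants out, or fill in their scores by MICE.

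- Leaving them out conditions on remaining at home.
- Filling them in under missing at random borrows the relation between baseline and 1-year K-ADL from those who remained at home.
- For the dead, any imputed score is a number for a state that does not exist.

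The study has no comparator, so nothing else in the design would expose a mean change that looks better than what happened to the enrolled participants. The Discussion intends the results to inform refinement of services and reimbursement policy.

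**Working it through.** **Step 1. Reproduce the plan's own figures (Sample size).** The section says "approximately 370 patients are expected to meet eligibility criteria". At 70% participation, 370 × 0.70 = 259, which the plan rounds to about 250. After 20% attrition, 250 × (1 − 0.20) = 200, as stated. The expected number without a 1-year score because of an event is 250 × 0.20 = 50.

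**Step 2. Set the event rules side by side.**

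| Event | Ends follow-up (Safety considerations) | Named in the 20% attrition (Sample size) | Non-responder (logistic model) | Specific rule for the primary change |
|---|---|---|---|---|
| Death | yes | yes | yes | none; general MICE sentence only |
| Facility admission | yes | yes, as institutionalisation | yes, if permanent | none; general MICE sentence only |
| Hospitalisation >30 days | yes | not named | not named | none; general MICE sentence only |

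The analytic sample of about 200 suggests exclusion. The overall cohort together with MICE suggests imputation. The non-responder rule keeps deaths and permanent institutionalisation in the logistic denominator, which fits 250 better than 200. If the assumed 35–45% response applies to the 200 completers (70–90 responders), the rate over 250 is 70/250 = 28% to 90/250 = 36%.

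**Step 3. Size of the bias.** Let p be the event share, m the mean change in those who stay under follow-up and d the mean change in living participants with an event. The mean over both groups is (1 − p)m + pd, so the estimate based on m alone is off by m − [(1 − p)m + pd] = −p(d − m). The documents give no K-ADL change and no SD, so d − m is an assumption.

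| d − m (assumed) | Bias at p = 0.20 |
|---|---|
| 0 | 0 |
| 1 | −0.2 |
| 2 | −0.4 |
| 3 | −0.6 |
| 4 | −0.8 |

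The sign can matter. With m = −0.5 (assumed) and d = +1, +2, +3 or +4, the combined mean 0.8 × (−0.5) + 0.2 × d is −0.2, 0.0, +0.2 or +0.4.

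The 20% includes deaths, for which d is undefined, and the split is not given. If half of the 50 died (assumption), the living cohort is 225 and p = 25/225 = 0.11, so the same 1 to 4 points gives a bias of 0.11 to 0.44.

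**Step 4. Does MICE repair it?** A simulation assumed n = 250, baseline mean 13 and SD 3, SD of change 2.5 and about 21% events. It drew 20 imputations per run from a regression on baseline K-ADL, over 500 runs.

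| Extra worsening after an event | Whole cohort | Completers only | MICE |
|---|---|---|---|
| 0 points | +0.05 | +0.07 | +0.05 |
| 3 points | +0.63 | +0.08 | +0.06 |

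MICE nearly reproduces the completers' answer. The simulation gives every event participant a 1-year score, so it speaks only for the living, and it uses no auxiliaries beyond baseline K-ADL. Richer auxiliaries may capture decline before the event. They cannot supply the effect of the event itself, because no participant with an event has an observed 1-year K-ADL.

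**The case against.** The strongest reply is that this reads too much into a condensed article. The missing-data sentence is generic, and nothing says that MICE will be used for the dead or for the paired test. The figure of 200 comes from a sample-size paragraph based on feasibility and the secondary analyses, so it is not an analysis-set definition. The scope of imputation is often settled in the full protocol or analysis plan. The events are outcomes in their own right and will be reported, and the Discussion disclaims causal inference.

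Much of this stands. A reader might infer that the plan excludes event participants from the primary analysis, or that it imputes the dead; the text states neither. A reader might also infer that long-hospitalised participants are imputed in both analyses, but permanent institutionalisation is undefined and could cover some of them. Reporting the events separately does help.

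What the reply does not remove is the misfit among rules that the article does fix: follow-up stops at the event, the primary test claims the overall cohort, imputation is stated without exception, and event handling is confined to a secondary model. Both available routes lead to the same place, so the point does not depend on which one was meant. A later analysis plan can restrict imputation, but it cannot recover scores that were never collected.

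**Conclusion.** The point holds as an unresolved definition of the primary analysis with a likely direction of bias. About 50 of 250 participants are expected to have no 1-year K-ADL because of an adverse outcome. On either route the mean change describes those who stayed under follow-up. For deaths the problem is what is being estimated, since a bias in points has no meaning there. For living participants with an event, the bias is towards improvement if they worsen more than the others: 0.2 to 0.8 points for an assumed 1 to 4 points at a 20% share, less if deaths make up much of that share, and zero if there is no difference.

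A reader might go further and conclude that the primary result will be falsely favourable by several standard errors. The documents do not support that: they give no SD, no expected change and no split of the 20%. The direction is plausible because the events mark decline and the plan itself counts death and permanent institutionalisation as non-response, but the size is illustrative.

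**What to change.** In Statistical analysis:

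1. Exclude decedents from K-ADL imputation. Limit MICE under missing at random to participants without a follow-up-ending event whose 1-year score is missing.
2. Label the paired-test result as the change among participants who remained under follow-up at 1 year, not the overall cohort. This label needs no vital status at 1 year, which the stop rule in Safety considerations does not secure after a non-fatal event.
3. Report beside it, as a supportive analysis, a summary of all enrolled participants (improved, unchanged, worse, hospitalised >30 days or institutionalised, died) with a 95% CI.
4. Align the non-responder rule with the event list in Safety considerations, so that every event that ends follow-up, including hospitalisation >30 days, is handled the same way.
5. Add a shift (delta-adjusted) sensitivity analysis of the K-ADL change for living participants with a non-fatal event. The shifts must be assumed and fixed in advance, because no post-event scores are collected.

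The cost is revised wording, one further table and one sensitivity analysis, with a possibly less favourable headline. No extra patients are needed. Enrolment began on November 5, 2025 (Status and timeline), so the first 1-year assessments fall due around November 2026; the change is best made before then.

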### Ethics and dissemination

This protocol was approved by the Public Institutional Review Board (IRB) designated by the Ministry of Health and Welfare (No. P01-202510-01-034; October 21, 2025) and will be conducted in accordance with the Declaration of Helsinki. The protocol is also registered with the Clinical Research Information Service (CRIS) (No. KCT0011283; Protocol Version 1.4, December 9, 2025; URL: https://cris.nih.go.kr/cris/search/detailSearch.do?seq=31625&search_page=L). The full study protocol is provided in the Supplementary Materials (**S2** and S3 Files. Study protocol for IRB).

Written informed consent will be obtained from all participants; for those unable to consent, consent will be obtained from legal representatives. Participants will be asked to provide optional consent for sharing de-identified data with NIKOM for secondary analyses; refusal will not affect participation. All data will be de-identified using unique study codes. The re-identification key will be stored separately at each site in a locked cabinet or password-protected computer, accessible only to authorized investigators. As described in the informed consent form, de-identified individual participant data will be shared with the National Institute for Korean Medicine Development, retained for up to 10 years, and may be linked with public databases such as the National Health Insurance Service database for secondary analyses to inform policy development. Findings will be disseminated through peer-reviewed publications.

### Status and timeline

The study is currently recruiting. Participant enrollment began on November 5, 2025, and will continue until October 20, 2026. Data collection is scheduled to conclude by October 20, 2027.

## Discussion

This paper describes the protocol for the K-HOME registry, a multicenter prospective registry established within the LTC-HMC pilot project in South Korea. The registry aims to evaluate longitudinal changes in ADL and AIP-relevant outcomes among homebound older adults receiving services through KM-HMCs.

The registry is designed to address evidence gaps in KM home care. Compared with prior reports that were largely small in scale [25–27], this study will collect standardized longitudinal data on functional status and key events such as institutionalization and mortality over 1 year. By capturing routine practice, the registry may complement evidence from controlled trials and support evaluation of real-world service delivery across diverse patient profiles and practice patterns [28–30]. The registry will also describe the delivery of KM interventions and interprofessional team-based care within the participating sites.

Several limitations should be considered. First, the observational design without a control group limits causal inference. To mitigate confounding, analyses will adjust for prespecified covariates using multivariable models. Second, although sites were selected to capture geographic variation, participating centers and patients may not represent all home care users nationwide; standardized procedures and centralized data management are intended to improve consistency and reduce measurement bias. Third, participants are restricted to those with Long-Term Care Insurance grades 3–4, which may limit the generalizability of the findings to individuals with milder or more severe functional impairment.

The K-HOME registry provides an initial framework for longitudinal evaluation of KM home care in the LTC-HMC context. Future extensions may include broader eligibility (e.g., Long-Term Care Insurance grades 1–2) and additional measures appropriate for severe functional impairment and end-of-life care, as well as expansion of participating sites. Over time, registry data may inform the refinement of service delivery and contribute to real-world evidence to support standardization and reimbursement policy discussions in a super-aged society.
